#### Development of the Evaluation Plan

##### Study Design

The evaluation of the IHS program is designed as a pilot randomized controlled trial. For recruitment, officially registered preschools in the Provincial Education Department database are stratified according to the socioeconomic status of people living in that area. The three levels of high, middle, and low socioeconomic areas are defined according to the categorization of the Provincial Education Department. Two preschools are randomly selected from each socioeconomic level (a total of 6 centers) and then allocated to the intervention and control groups (Figure 1). Overall, 3 centers in the intervention group (each center belongs to a different socioeconomic level) and 3 centers in the control group are defined. The selected centers are contacted in person and provided with comprehensive information. After confirmation of managers, 2 classes are randomly selected for enrollment (6 classes in the intervention group and 6 classes in the control group). Then, the parents of eligible children are invited in a meeting in preschool, and informed consent is obtained after a brief introduction on the whole program and the role of parents (for parents of the intervention group) and informing parents for data collection and cooperation in filling questionnaires (for parents of the control group). The components of the intervention program for managers, educators, children, and parents are conducted in intervention classes, and control classes receive the conventional preschool education program. Aiming to acknowledge the cooperation of control preschools, the wait-list approach is suggested to the managers to receive the intervention in the next educational year, as well as a comprehensive report for growth, nutrition, and physical activity status of each child, which is given after the intervention, is completed.

The intervention lasts for 6 months. The duration of an educational year in preschools in Iran is the same as elementary schools and lasts for 8 months (October-May). From March 21, there are around 2-week New Year (Norouz) holidays. The intervention will be completed before Norouz holidays. The required data are collected at baseline and after the completion of the intervention period.

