###### Nutrition Risk

The NutriSTEP [33,34] has been first designed and validated in Canada in different languages for assessing eating habits and nutrition problems in children aged 3-5 years. A license was obtained from the developers of NutriSTEP questionnaires. The Persian version of NutriSTEP was used after translation and cross-cultural adaptation [35]. The NutriSTEP scoring system categorizes children into low, medium, and high risk in terms of nutritional status. It covers 4 main domains related to children’s food intake as follows: (1) food and fruit intake; (2) physical growth and development; (3) factors affecting the food intake and eating behavior; (4) physical activity and sedentary behavior.

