##### Data Analysis

Descriptive analysis (frequency, percentage, mean, and SD) will be used to characterize and compare the basic characteristics of participants in the intervention and control groups. Outcomes related to nutrition and physical activity will be compared between the intervention and control groups to seek any possible improvements following the intervention. Considering the number of intervention (n=152) and control (n=148) participants, which anticipates a normal distribution, independent sample *t* test, and chi-square tests will be used for between-group comparisons, while paired sample *t* test and MacNemar tests will be used for analyzing within-group changes. Any possible covariates will be controlled with the analysis of covariance test. All tests are 2-tailed, and a significance level of <.05 will be considered statistically significant. Data analysis will be done by IBM SPSS Statistics for Windows, version 23.0 (IBM Corp).

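### The plan does not say which analysis decides the effect: unadjusted between-group tests and within-arm paired tests share one .05 threshold, although a single baseline-adjusted between-arm comparison could be made with data already collected

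*Protocol article*

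**What the plan says.** All of the following is in the protocol article.

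- **Comparison of interest (Data Analysis):** "Outcomes related to nutrition and physical activity will be compared between the intervention and control groups to seek any possible improvements following the intervention".
- **Between-group tests (Data Analysis):** the independent-sample t test for means, and "chi-square tests will be used for between-group comparisons". No covariate enters either test.
- **Within-group tests (Data Analysis):** the paired t test, and "MacNemar tests will be used for analyzing within-group changes".
- **Adjustment (Data Analysis):** "Any possible covariates will be controlled with the analysis of covariance test". Neither the baseline value nor the socioeconomic level is named.
- **Threshold (Data Analysis):** "All tests are 2-tailed, and a significance level of <.05 will be considered statistically significant".
- **Design (Study Design):** "officially registered preschools in the Provincial Education Department database are stratified according to the socioeconomic status of people living in that area". Two preschools come from each of three levels, one per arm, so there are six centres. Data are collected at baseline and after the 6-month intervention.

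The section does not say whether the t test is run on end values or on changes. It also does not rank the unadjusted, adjusted and within-arm analyses.

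**The concern.** Three kinds of analysis are named for the same outcomes under one significance level, and none is given precedence. Two problems follow.

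First, a paired test within one arm asks whether children changed, not whether the programme changed them. Children aged 4-6 grow and mature over 6 months, so weight, height, waist and arm circumference will rise in both arms, and attitude scores may drift. A significant change in one arm beside a non-significant change in the other is not a comparison of arms, though it is easily reported as one.

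Second, each child's baseline value is available and usually predicts the end value, but the named between-group tests do not use it as a covariate. ANCOVA serves continuous outcomes only, so outcomes that go to the chi-square test have no adjusted analysis at all.

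**Working it through.** The article gives no power calculation, effect size, SD or baseline-end correlation, so there is no stated figure to reproduce.

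**Inputs.** From Data Analysis: 152 intervention and 148 control children, two-sided .05. Assumed, because the article gives no values: child-level baseline-end correlation r of 0.5, 0.7 or 0.9, equal SDs at baseline and end, and a trend common to both arms of 0 to 0.3 SD. Both calculations treat children as independent.

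**1. Within-arm tests when the programme has no effect**

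The SD of change is sqrt(2(1 - r)). The paired test has noncentrality trend × sqrt(n) / SD of change. With independent arms, P(intervention significant, control not) = P(intervention significant) × [1 - P(control significant)].

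Example: r = 0.5, trend 0.15 SD.
- SD of change = sqrt(2 × 0.5) = 1.
- Intervention: 0.15 × sqrt(152) = 1.85, so P(significant) = 0.456.
- Control: 0.15 × sqrt(148) = 1.82, so P(significant) = 0.446.
- Misleading pattern: 0.456 × (1 - 0.446) = 0.25.

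| Common trend (SD) | r = 0.5 | r = 0.7 | r = 0.9 |
|---|---|---|---|
| 0 | 0.048 | 0.048 | 0.048 |
| 0.10 | 0.181 | 0.232 | 0.176 |
| 0.15 | 0.252 | 0.230 | 0.017 |
| 0.20 | 0.221 | 0.106 | 0.000 |
| 0.30 | 0.044 | 0.003 | 0.000 |

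The ceiling is about 25%, because p(1 - p) peaks at 0.25 when each test has 50% power. The low values at large trends give no reassurance: there both arms are almost always significant, still with no programme effect.

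**2. Precision of the between-arm comparison**

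Relative to an end-value t test, the variance is 1 - r² for ANCOVA and 2(1 - r) for a t test on changes. The detectable difference at 80% power is (1.960 + 0.842) × sqrt(1/152 + 1/148) × sqrt(variance factor), which is 0.324 SD × sqrt(variance factor).

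| r | End value: factor; detectable | Change: factor; detectable | ANCOVA: factor; detectable |
|---|---|---|---|
| 0.5 | 1.00; 0.324 SD | 1.00; 0.324 SD | 0.75; 0.280 SD |
| 0.7 | 1.00; 0.324 SD | 0.60; 0.251 SD | 0.51; 0.231 SD |
| 0.9 | 1.00; 0.324 SD | 0.20; 0.145 SD | 0.19; 0.141 SD |

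Whole centres are allocated, so the detectable differences are optimistic in absolute terms. The comparison between columns is the point.

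**3. Adding the socioeconomic stratum**

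A centre-level comparison has 6 - 2 = 4 degrees of freedom. Two stratum terms leave 2. The 95% t critical value goes from 2.776 to 4.303, a factor of 1.55. To break even on interval width, the strata would have to remove 1 - (2.776/4.303)² = 0.58 of the variance.

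**The case against.** The strongest reply is that the plan is better than a quick reading suggests, and much of it stands.

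- **Effects judged from within-arm tests.** A reader might infer this, but the article does not say it. It states a between-arm comparison of interest and assigns the paired tests to within-group change only.
- **Growth biasing the main comparison.** It does not. A trend common to both arms cancels in a between-arm test. BMI percentile and z-score are also standardised for age.
- **No adjustment planned.** Adjustment is planned, through ANCOVA. An article may leave the covariate list to a fuller document, so the missing list alone is not the point. The point is that the article fixes unadjusted tests as the comparison and does not say which analysis decides.
- **Large loss of precision.** This depends on testing end values. The Abstract describes outcomes as changes, and against a change-score test the gain is modest at high correlation.
- **Baseline imbalance passing into the result.** With about 50 children per centre and an assumed ICC of 0.05, the design effect is 1 + 49 × 0.05 = 3.45 and the chance imbalance has SD sqrt(2 × 3.45/150) = 0.21. At r = 0.7, about 0.7 × 0.214 = 0.15 SD carries into an end-value test, but only about 0.3 × 0.214 = 0.06 SD, in the opposite direction, into a change-score test. The ICC is not in the document, and a correct clustered standard error already covers this variation.
- **A misleading pattern half the time.** That counts either arm alone being significant. The direction that would favour the programme occurs at most about 25% of the time.
- **McNemar misapplied to NutriSTEP.** The article says "The NutriSTEP scoring system categorizes children into low, medium, and high risk in terms of nutritional status", and standard McNemar needs binary pairs. But Data Analysis does not assign that test to the three-level category, and a score or a dichotomy could be what is tested.

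**Conclusion.** The concern holds in a limited form. The article names unadjusted between-group tests, leaves ANCOVA open-ended, gives within-arm tests the same threshold and does not say which result decides. Within-arm p-values cannot show a programme effect. With no effect, the misleading pattern has a probability from about 0 to 25% over common trends of 0 to 0.3 SD, and 4.8% with no trend.

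Baseline adjustment improves precision over either t test under the assumed correlations. The gain is large against end values (variance factors 0.75, 0.51 and 0.19) and smaller against changes (0.75 against 1.00, 0.51 against 0.60, 0.19 against 0.20). These are child-level figures that rest on assumed correlations.

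The documents do not support the claim that conclusions will be drawn from the paired tests, or that growth biases the between-arm comparison. Adjustment for stratum reflects the design, but with six centres it is a trade-off and not a free gain.

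**What to change.** In Data Analysis, state one inferential comparison for each outcome: the between-arm difference at end, adjusted for the child's own baseline value and accounting for centre clustering.

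- **Continuous outcomes:** ANCOVA on the end value with baseline as covariate.
- **Categorical outcomes:** a baseline-adjusted logistic model, or an ordinal model where the categories are ordered. If the three NutriSTEP categories are analysed as such, the ordinal model applies.
- **Within-arm change:** report means, SDs or percentages by arm, and drop the paired t and McNemar p-values.
- **Other covariates:** name them in advance and label any further adjusted analysis as supportive.
- **Socioeconomic stratum:** decide explicitly whether it enters, given the fall from 4 to 2 centre-level degrees of freedom, and record the reason.

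The cost is wording and a modest change of model, since baseline and end values are already collected. The Results section says that analysis is under way, so the choice should be fixed and dated before results are reported.

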**Methods:**

We will evaluate the intervention using a pilot randomized controlled design. The components of intervention include customized Decoda Web-based resources for children, an implementation guide for educators and managers, training and monitoring, communication and knowledge exchange, building partnership, and parent engagement. Outcomes include changes in anthropometry, physical activity level, nutritional risk status and dietary intake, and quality of life.

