##### Participants and Data Collection

In the Iranian preschool bylaws, preschool is not a mandatory level, and all children aged 4-6 years can be registered either in preschool-1 (age, 4-5 years) or preschool-2 (age, 5-6 years). All children aged 4-6 years of the selected classes of each center are included in the study after a valid consent from their parents or legal guardian, while those with known chronic disease, such as cardiovascular, respiratory, endocrine, or musculoskeletal problems—after physician inquiry—as well as those who need to adhere to a specific diet, such as gluten-free or phenylalanine-free diets, are excluded.

Data reflecting the nutrition status, diet quality, physical activity and sedentary behaviors, quality of life, and anthropometry of children, as well as the general sociodemographic status of participants and their families are collected at baseline and after the intervention is completed (Table 3). Data collection is performed by a team of 4 nutritionists who are given comprehensive training to standardize the data collection. They learned how to consistently obtain anthropometric measurements, fill the required questionnaires, and train the use of pedometers and filling the parent-report questionnaires to parents. Data entry is done by one person for consistency (a PhD student). Each preschool takes about 7-10 days to collect all the required data. As parents’ cooperation is very important in the data collection, aiming to acknowledge their cooperation, especially in control preschools, a gift for children and a free nutrition consultation for children and their parents, as well as a comprehensive report for child growth, nutrition, and activity status, are dedicated.

As this is a pilot study and we cannot estimate the attrition rate, there is no need to define the sample size, but sample characteristics represent the population of preschool children in Mashhad.

**Table 3 table3:** Overview of the study process.

Group and action		Months	

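### ANCOVA is the only covariate adjustment named; if nutrition risk is analysed as low/medium/high, the plan offers no suitable adjusted method

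*Protocol article*

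**What the plan says.** The Abstract lists the outcomes: "Outcomes include changes in anthropometry, physical activity level, nutritional risk status and dietary intake, and quality of life". The Nutrition Risk section describes the tool: "The NutriSTEP scoring system categorizes children into low, medium, and high risk in terms of nutritional status". Table 4 records nutrition risk at baseline and at the end.

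For categorical data, the Data Analysis section says that "chi-square tests will be used for between-group comparisons" and that "MacNemar tests will be used for analyzing within-group changes". The adjustment sentence is "Any possible covariates will be controlled with the analysis of covariance test". It exempts no type of outcome, and no ordinal, logistic or other adjusted model for categories appears. The error rate is set by "All tests are 2-tailed, and a significance level of <.05 will be considered statistically significant", and the arm sizes by "Considering the number of intervention (n=152) and control (n=148) participants".

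The article does not say whether nutrition risk is analysed as the numeric NutriSTEP score, as the three levels, or as both. It does not name the covariates. It gives no power, effect size or category proportions, and holds that "there is no need to define the sample size".

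**The concern.** The plan promises to control covariates for its outcomes but names a tool that fits only the quantitative ones. For a three-level outcome the promise can be met only by scoring the levels (say 1, 2, 3) and treating the steps as equal. Otherwise it is not met, and the unadjusted chi-square test stands.

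Two things are at stake. The child's own baseline level, which is collected anyway, is the strongest predictor likely to be available, and leaving it out costs precision. In addition, only three preschools are allocated to each arm, so the arms may well differ at baseline. An unadjusted comparison at the end carries that difference into the result.

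**Working it through.** **Inputs from the protocol article.** 152 and 148 children; two-sided 5% level; three ordered risk levels; six preschools, three per arm (Study Design).

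**Assumed inputs, not in the article.** Split of 60/30/10 across low/medium/high; latent normal risk with baseline-to-end correlation r of 0.5 to 0.7; true effect of 0.3 SD; baseline gap of 0.2 to 0.3 SD; intraclass correlation (ICC) of 0.02 to 0.10; 300/6 = 50 children per preschool. The plan states no figure of its own to reproduce.

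**Step 1, power of the chi-square test.** The cut-points are z = 0.253 and 1.282. A shift of 0.3 SD towards lower risk changes 0.600/0.300/0.100 to 0.710/0.233/0.057. The noncentrality is

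λ = (n₁n₂/N) Σ (p₁ − p₀)²/p̄ = (152 × 148/300) × (0.01845 + 0.01680 + 0.02380) = 74.99 × 0.0590 = 4.43.

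On 2 degrees of freedom at 5% this gives power of about 45%. A shift the other way gives λ = 4.92 and about 50%.

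**Step 2, power with adjustment, by simulation.** 400 to 500 trials per scenario where the count is known, children independent, no baseline gap, r from 0.5 to 0.7:

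| Analysis | Power at 0.3 SD, separate runs |
|---|---|
| Chi-square | 43–45%, 41–46%, 47–49% |
| Ordinal, unadjusted | 53–54%, 55–57% |
| Proportional odds with baseline category | 58–72%, 64–72%, 69–73% |
| ANCOVA on codes with baseline code | 65–71% (one run) |

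The chi-square row agrees with Step 1. Respecting the order recovers part of the loss. The baseline category recovers more, chiefly when r is high.

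**Step 3, no effect but an imposed baseline gap, children independent.** The expected end-of-study gap is r × baseline gap, from 0.5 × 0.2 = 0.10 SD to 0.7 × 0.3 = 0.21 SD. The Step 1 formula with these shifts gives λ = 0.52 to 2.23 and rejection of about 9% to 25%. Simulation gave 8–26% in one run, and 9–28%, 10–28% and 9–31% in repeats. Proportional odds with baseline category gave 4–8% across the runs. With no imposed gap, chi-square gave 3–7%, close to nominal.

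**Step 4, whether such a gap is plausible.** With three preschools of 50 per arm,

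SD of gap = √[2(1 + 49 × ICC)/150].

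ICC 0.02: √(2 × 1.98/150) = 0.16. ICC 0.10: √(2 × 5.90/150) = 0.28. This is before any gain from socioeconomic stratification, so a gap of 0.2 to 0.3 SD would not be unusual.

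**Step 5, whether baseline adjustment is enough under clustering.** Simulation with six preschools of about 50 children and no programme effect:

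| Latent ICC | Chi-square rejects | Proportional odds with baseline category rejects |
|---|---|---|
| 0.02 | 10% | 10–12% |
| 0.05 | 19–24% | 21–28% |
| 0.10 | 31–33% | 30–31% |

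The baseline category alone does not bring the error rate back to 5%. It helps only to the extent that preschool differences persist from baseline to end.

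**The case against.** Four objections carry weight.

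- **A third route exists.** NutriSTEP is described as a scoring system, so a score lies behind the levels. ANCOVA on that score, with the baseline score as covariate, fits the plan as written. A reader might infer that nutrition risk must be tested either unadjusted or on arbitrary codes. The article does not support that: it neither commits to the score nor rules it out. McNemar in its usual form is for two-level data, so naming it does not show that a three-level endpoint is planned. Codes for low/medium/high would also be ordered, so they are not arbitrary; what is assumed is their spacing. In the simulation, codes with a baseline code did about as well as proportional odds, so the objection to them is interpretability more than error rate.
- **Unadjusted is not invalid.** A reader might take the 8–31% in Step 3 as the type I error of the planned test. It is not. It is conditional on a chosen gap, and with independent children and no gap the chi-square test is about nominal.
- **Adjustment does not cure clustering.** Step 5 shows this. The 4–8% and the power gains assume independent children and do not carry over to six allocated preschools.
- **It may be a matter of condensation.** An article can leave model detail to an analysis plan. That would excuse silence. Here the text fixes one method for all covariates, just after assigning tests to categorical outcomes that the method does not suit. That part stands as something fixed badly.

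**Conclusion.** The point holds in conditional form. ANCOVA is the only adjustment named and it does not suit categorical outcomes. If nutrition risk is analysed as low/medium/high, the stated plan gives either an unadjusted chi-square test that ignores order and baseline category, or ANCOVA on codes with assumed spacing.

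The cost is mainly precision. At 0.3 SD, power is roughly 43–49% for chi-square (the lowest repeat was 41%) against 58–73% for baseline-adjusted proportional odds. These figures rest on the assumed 60/30/10 split, r of 0.5 to 0.7 and independent children. Any baseline gap between the arms also stays in the unadjusted result, but the size of that harm depends on a gap the article does not give.

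The documents do not show that the planned test is invalid, that nutrition risk will be analysed only by category, or that baseline adjustment alone would give a sound p-value in this design.

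**What to change.** Replace the adjustment sentence with text that does the following:

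1. States whether the NutriSTEP score, the category or both are analysed.
2. For the score and other quantitative outcomes, uses ANCOVA with the baseline value.
3. For categories, uses proportional-odds regression (three levels) or logistic regression (two levels), with the child's baseline category and the socioeconomic stratum.
4. Accounts for allocation by preschool in the same model, for every outcome.

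Items 1 to 3 need a few lines of text, standard regression procedures and no new data. The downside is small: results become odds ratios, and the proportional-odds assumption has to be checked. Item 4 costs more. Six preschools less two arms leave at most 6 − 2 = 4 degrees of freedom for the between-preschool comparison, and with three strata in the model 6 − 1 − 1 − 2 = 2. Power will therefore be below the figures above, and the results should be presented as those of a pilot.
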